**Figure 1 F1:**
[figure not shown]
Schematic outline of the main study.

The sample size has been estimated based on previous local data [12,26]. Estimated changes to the utilization of therapy are founded in data from previous studies where only 35% of high-risk AF patients were prescribed warfarin, where interventions have demonstrated upgrades in therapy in poorly protected patients by at least 15% to 23% [12,26]. Taking into account any clustering effects (*a prior* intra-cluster correlation/ICC = 0.03), and a participant drop-out rate of up to 20%, a minimum of 25 GPs and 250 patients are required to achieve statistically significant results [32,33].

### Participant recruitment and eligibility

a) General Practitioner

GPs will be recruited via invitational letters, promotional flyers inside newsletters, and presentations during education events, coordinated by the Divisions of General Practice. Eligible GPs include those who:

•are practicing in one site at a general practice surgery and not across multiple sites or surgeries;

•practice in the specified Divisions of GP;

•provide informed written consent to participate in the study.

Once recruited, the GPs will be randomly allocated to a study arm (‘intervention’ versus ‘control’) using computer-generated random allocation number sequences. The process will be coordinated centrally by a Chief Investigator independently of GP recruitment, intervention implementation, or data collection processes, and who will conceal the initial allocation process from project officers (e.g., allocation numbers will be placed in sealed, serially coded envelopes, and housed in a locked cabinet).

b) Patient

Patients will be recruited by their GPs during routine care over a 3-month period. Each GP will be required to recruit 10 patients that meet the following study inclusion criteria:

•are aged ≥ 65 years;

•have a diagnosis of chronic (persistent) AF, whether new or pre-existing and irrespective of the antithrombotic therapy prescribed at the time of recruitment;

•provide informed written consent to participate in the study and agree to be followed-up via telephone interview over a 12 month period (1,6 and 12 months).

Patients will be informed that all personal information is de-identified and that they may withdraw from the study at any time without any negative consequences.

In using the cluster-randomized trial design, contamination *within* groups of GPs is minimized. Any contamination *between* groups will be minimized through specific screening during the recruitment process to exclude those GPs practising across multiple (≥1) surgeries. Within ‘group’ practices (e.g., medical centres where more than 1 GP is employed), all participating GPs will be allocated to the same study arm (block randomisation). Once allocated, drop-ins between arms and sharing of the ‘intervention (i.e., password protected CARAT) will not be permitted.

### Intervention Arm

The CARAT will be disseminated via a web-based interface to GPs randomized to the intervention arm. Upon recruitment, GPs will be given access to CARAT via log-ins, passwords, together with supporting information and on-site training by the project officer.

During routine clinical practice, GPs will utilize the CARAT to support their decision-making processes in selecting and/or reviewing antithrombotic therapy in their patients. This will involve performing an individualized risk assessment and generating a treatment recommendation for their patient by carefully assessing relevant risk factors for stroke, bleeding, medication misadventure and entering this data, as guided by CARAT, into the web-based platform. CARAT will then quantify the patient’s estimated risk of stroke versus bleeding, flag pertinent medication management issues, and generate a recommendation for therapy (warfarin, aspirin, none, other). *Note: CARAT does NOT require identifiable personal information to be entered NOR is any information saved to the website.*

The GP will consider the CARAT output and make a final treatment decision to initiate, cease, or maintain current antithrombotic therapy. Where the GP may disagree with CARAT, the rationale for the decision will be documented in the data collection process. Reviewed patients will be followed-up for up to 12 months to document key clinical outcomes (i.e., strokes, bleeds).

### Control Arm

GPs randomized into the control arm will follow their usual care practices. They will review and select antithrombotic therapy using their own clinical judgment, processes and resources. At completion of the study (i.e., final patient follow-up period at 12 months is complete), the GPs in the control arm will be given the opportunity to trial the CARAT on 5 of their patients in their practice setting (‘cross-over’ arm) to canvas feedback on the tool.

### Data collection

In addition to the output generated by CARAT, purpose-designed data collection instruments (record forms, surveys, questionnaires) will be used to extract and record specific data (Table 1). Dedicated Project Officers will be allocated to each participating division of general practice, to coordinate the conduct of the study (i.e., participant recruitment, implementation of intervention, data collection, provision of support to GPs) at each site.

**Table 1 T1:** Data collection items for GPs and patients

**GPs**	**Patients**
• Demographics (age, gender)	• Patient demographics
• Practice experience (years, specialty)	• Medical history, co-morbidities, medication
• Practice site features (location, number of clients)	• History of AF (duration, new onset or chronic)
• Decision-making processes (e.g., resources or processes normally used)	• Risk factors for stroke (per CARAT)
• Agreement with CARAT recommendations (Intervention group)	• Risk factors bleeding (per CARAT)
• Satisfaction with CARAT as a tool (Intervention group)	• Quality of life (e.g., SF36)
• Barriers to prescribing therapy (ALL GPs)	• Risk factors for medication misadventure [25]
	• Current antithrombotic therapy utilised
	• History of clotting and bleeding events
	• Health services used to support therapy
	• Health services used to support therapy

Baseline data for patients and GPs will be collected by the project officer within 48 hours of the index consultation. During the baseline visit, the GP will apply CARAT to consecutive admissions over a period of 3 months and obtain the patient’s consent to participate. GPs will print-out the completed risk-assessment template (generated by the CARAT) for subsequent review by the project officer. Each GP will then ‘flag’ the patient for review and baseline data collection by the project officer by returning a purpose-designed fax-back form with basic patient details. Baseline data will be extracted from medical notes, patient interview, and a brief patient survey.

Clinical outcome data will be collected at 1, 6 and up to 12 months after the index consultation. This data will be collected from patients via follow-up telephone interview (15–20 minutes) by the project officer. To verify outcomes, the GP will be contacted via phone and/or the patient’s notes reviewed. Hospital medical records may also be reviewed where patients have been admitted for an acute event including a stroke or bleed.

A 1-month pilot study will be conducted prior to the main trial to confirm project procedures/logistics.

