### Participants

Fifty GPs will be recruited and randomized to either the intervention (CARAT) arm or control (usual care) arm to recruit a total 500 elderly patients with AF (Figure 1), i.e., 25 GPs will be recruited to each of the two study arms. Randomization will occur at the GP level at the time of recruitment [31], not at the division or regional level, to facilitate comparison over a cross-section of GPs and patients, and to negate any regional confounders.

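### GP baseline data are timed to the index consultation, after allocation and CARAT training, so GP-reported usual decision processes (and barriers, if taken then) would not be pre-exposure values in the intervention arm

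*Protocol article*

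**What the plan says.** The protocol article places four steps in the path of an intervention GP.

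- **Allocation** (Participants): "Randomization will occur at the GP level at the time of recruitment".
- **Disclosure** (Minimizing selection bias and contamination): GPs first receive only generic information. The hypotheses and the tool are explained to Group A once allocation has been made.
- **Access and training** (Intervention Arm): "Upon recruitment, GPs will be given access to CARAT via log-ins, passwords, together with supporting information and on-site training by the project officer".
- **Baseline collection** (Data collection): "Baseline data for patients and GPs will be collected by the project officer within 48 hours of the index consultation". The same section describes the consultation itself: "During the baseline visit, the GP will apply CARAT to consecutive admissions over a period of 3 months and obtain the patient’s consent to participate". The GP then prints the output, and "Each GP will then ‘flag’ the patient for review and baseline data collection by the project officer by returning a purpose-designed fax-back form".

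The GP column of Table 1 lists, among other items, "Decision-making processes (e.g., resources or processes normally used" and "Barriers to prescribing therapy (ALL GPs". It also lists "Satisfaction with CARAT as a tool (Intervention group", which can be answered only after use. The table gives no time point for any item.

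The abstract says that participant characteristics and relevant practice and clinical parameters are recorded at baseline. It names neither decision processes nor barriers.

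**The concern.** A baseline value has to be taken before the participant can be affected by the intervention. In a cluster trial the GP is both the unit allocated and the person whose behaviour is to change, so this applies to GP-level measurements as much as to patient-level ones.

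Two GP items are of the kind that CARAT is meant to alter. One asks how the GP usually reaches a decision and with what resources. The other asks what hinders prescribing. The Background names misperceived risk and anxiety about causing harm as targets for support to GPs, and the Intervention Arm section presents the tool as an aid to decision-making. A GP who has been told the hypotheses and trained on the tool may answer both questions differently from one who has not, and only intervention GPs have had that exposure. The project officer who collects the answers also gives the training.

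At stake is the meaning of these items. Reported as baseline, they could show an apparent imbalance between arms that the intervention itself produced, or conceal a real one. Entered as baseline covariates in a model for choice of therapy, they could bias the estimated effect of CARAT. A pre-exposure value cannot be recovered afterwards.

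**Working it through.** No arithmetic applies: the question is the order of events, and it depends on no sample size, power or significance level. The article gives no figure to reproduce. The check sets the sections in sequence and then tests how much depends on inference.

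**Step 1. Sequence by arm**

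| Step | Intervention GP | Control GP | Source |
|---|---|---|---|
| 1 | Recruited and randomized | Recruited and randomized | Participants |
| 2 | Told the hypotheses and about CARAT | Generic information only | Minimizing selection bias and contamination |
| 3 | Log-in, supporting material, on-site training | None | Intervention Arm; Control Arm |
| 4 | Index consultation, CARAT applied | Index consultation, usual care | Data collection; Control Arm |
| 5 | Print-out, patient flagged by fax-back form | Patient flagged | Data collection |
| 6 | Project officer collects baseline data | Project officer collects baseline data | Data collection |

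The sentence on applying CARAT at the baseline visit names no arm. Read with the Control Arm section, I take it to concern the intervention arm only.

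**Step 2. Does the result depend on reading the 48-hour window as after the consultation?** The wording does not say before or after.

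- *Collected after the consultation:* steps 2 to 4 have all happened, so the GP has been informed and trained and has used the tool at least once.
- *Collected shortly before it:* steps 2 and 3 have still happened, because they follow from recruitment and not from a patient visit.

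On either reading, GP baseline data in the intervention arm follow disclosure and training. Only the further claim, that they follow first use, rests on the order of flagging and then collecting, and that order is described for the patient. For GP data it is probable, not stated.

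**Step 3. Which GP items can be affected?**

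| Table 1 GP item | Can training or use change the answer? |
|---|---|
| Demographics, experience, site features | No |
| Usual decision processes | Yes; the item asks for habitual practice, but recall can be coloured |
| Barriers to prescribing (both arms) | Yes, if taken at this contact |
| Agreement and satisfaction with CARAT | Meaningful only after use; not a baseline matter |

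**Step 4. Which planned results depend on the affected items?** The five primary measures in Outcomes measured concern therapy changes, the proportions on no therapy, on any antithrombotic and on warfarin, and adverse clinical outcomes. The three secondary measures concern sustained therapy, clotting events and bleeding events. None uses a GP process or barrier item. The logistic regression in Data analysis looks for predictors of events and of therapy selection but names no GP item, and the examples of predictors in the Discussion are risk factors and the antithrombotics prescribed.

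**Step 5. Extent.** The plan has 25 GPs per arm, so the affected answers are those of up to 25 of 50 GPs. The article holds no data from which the shift in those answers could be estimated.

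**The case against.** The strongest reply is that the article never calls these two items baseline. Table 1 covers the whole study, since it holds items that can exist only after use. The barriers item stands directly below two such items, so it may be an end-of-study question put to both arms. The sources that the Data collection section gives for baseline data (notes, patient interview, patient survey) do not include a GP questionnaire. This stands in part, and it is why the barriers item is included here only on condition that it is taken at the same contact. It is weaker for the item on usual processes, which by its wording asks for a state before any intervention, and the article states no other time for GP data.

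A reader might also infer more than the text supports:

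- *That the items cannot be compared between arms.* They can. After randomization, a difference by arm is a valid estimate of the effect of allocation. It is not a check of baseline balance.
- *That the plan uses them as predictors.* No section says so, so any harm to a regression is conditional.
- *That adjusting for them would pull the CARAT effect towards zero.* Adjustment for a variable affected by allocation can bias in either direction, depending on causes that the article does not describe.
- *That the data of the 250 intervention patients are compromised.* No patient measurement or outcome depends on when a GP answers these questions.
- *That ten patients per GP leave the GP data without a single date, and that this is itself a flaw.* The detailed schedule is something that an article commonly leaves to the full protocol.

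**Conclusion.** The point holds in limited form. As written, the GP baseline contact comes after disclosure and training in the intervention arm, and probably after first use. Answers on usual decision processes taken then, and on barriers if taken with them, are not pre-exposure values in that arm and should not be presented or modelled as baseline.

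The size is modest: one or two questionnaire items, up to 25 of 50 GPs, and consequences confined to descriptive and explanatory work. The primary and secondary outcomes and the fixed GP characteristics are not touched.

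The conclusion rests on two assumptions: that the stated 48-hour rule governs the item on usual processes, since no other time is given for GP data, and that training is delivered at recruitment as the Intervention Arm section says. If the full protocol takes these items at GP consent before allocation, the point reduces to correcting one sentence of the article. The change is worth making mainly because it is cheap and the information cannot be recovered later.

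**What to change.** 1. In Data collection, separate GP baseline from patient baseline. Keep the 48-hour window for patients. Collect GP characteristics, usual decision processes and barriers **once per GP at consent, before allocation is revealed and before any CARAT training**. In group practices, where all participating GPs go to one arm, obtain the answers before that practice's allocation is revealed.
2. Add a time point to each GP item in Table 1, and place agreement and satisfaction with CARAT after use.
3. State that only values taken before allocation count as baseline or may enter a model as baseline covariates.
4. If change in barriers is of interest, repeat that item at the end of follow-up, in control GPs before they are offered their trial of the tool, and report it as an outcome by arm.

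The cost is minimal: the same questions move to the existing GP consent contact, and the repeat in item 4 is optional. The change has to be in place before GPs are allocated. For any GP already allocated, report the answers as post-allocation data and leave them out of baseline tables and adjustment.

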### Data analysis

Computerized data analysis will employ SPSS (Statistical Package for the Social Sciences) Version 15. ANOVA will test for differences in continuous variables. The Chi-square test will examine differences in independent proportions. Kappa analysis will detect the level of agreement between prescribers’ clinical judgment and the CARAT output. Logistic regression analysis will identify predictors of clinical events (clotting versus bleeding), and selection of antithrombotic therapy, accounting for the use of the CARAT. Survival analysis will assess mortality rates in both arms. All analyses will necessarily be based on the ITT principle; standard imputation methods (e.g., last observation carried forward) will be used to estimate missing data (withdrawal, failure to start) and data analysed according to initial group (random) allocation. All analyses will be adjusted for the effects of clustering, and set at a significance (p) level of 0.05.

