### Outcomes measured

The primary outcome measures for the intervention will include:

•changes to therapy (initiations, changes, cessations) made following application of CARAT;

•difference in the proportion of patients receiving no therapy;

•overall difference in the proportion of patients receiving antithrombotic therapy;

•difference in the proportion of patients receiving warfarin therapy;

•difference in the proportion of patients experiencing adverse clinical outcomes (ALL events).

The secondary outcome measures will include:

•the sustainability of prescribed therapy over time, i.e., changes to antithrombotic therapy made during patient follow-up up to 12 months;

•incidence of any clotting (thromboembolism, stroke) events up to 12 months;

•incidence of any bleeding (minor or major hemorrhage) events up to 12 months.

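### Last observation carried forward is the only missing-data method named, and it allows no therapy change or clinical event after a patient's last contact

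*Protocol article*

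**What the plan says.** The Data analysis section of the protocol article states that "All analyses will necessarily be based on the ITT principle" and, in the same sentence, that "standard imputation methods (e.g., last observation carried forward) will be used to estimate missing data (withdrawal, failure to start"). LOCF is introduced as an example, but it is the only method named and no outcome is excluded.

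Under Outcomes measured, the secondary outcomes include "the sustainability of prescribed therapy over time, i.e., changes to antithrombotic therapy made during patient follow-up up to 12 months", the incidence of clotting events to 12 months, and "incidence of any bleeding (minor or major hemorrhage) events up to 12 months". The proportion of patients with any adverse clinical outcome (all events) is listed as primary.

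The sample-size paragraph under Participants allows for "a participant drop-out rate of up to 20" per cent. The Data collection section has outcomes gathered by telephone at 1, 6 and up to 12 months. GP contact or notes are used to verify outcomes, and hospital records may be reviewed after an acute admission.

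**The concern.** Sustainability is defined as change in therapy during follow-up. Carrying the last value forward assumes no change from last contact to month 12, so for patients who leave it assumes part of the answer. If an effect of the tool on prescribing wanes, intervention patients lost early stay at their early, more favourable therapy.

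The clotting, bleeding and all-events outcomes are cumulative to 12 months. For these, LOCF treats unobserved time as event-free. The Discussion section also promises absolute risks of stroke and bleeding in an Australian cohort, and those would be too low even if the two arms lost patients equally.

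**Working it through.** **Inputs from the protocol article.** Dropout of up to 20%. Target of 500 patients, where "25 GPs will be recruited to each of the two study arms" and each GP recruits 10. Control warfarin use: "only 35% of high-risk AF patients were prescribed warfarin". Improvement of 15 to 23 percentage points (read here as absolute). ICC 0.03. Contacts at 1, 6 and 12 months.

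**Assumed, because the article does not give them.** 80% power, a two-sided test, event and therapy-change rates, and the timing of dropout.

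**1. The plan's own figure.** The article says that "a minimum of 25 GPs and 250 patients are required to achieve statistically significant results". Read as per arm, for 35% v 50%:

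- n = (1.960 + 0.842)² × (0.35×0.65 + 0.50×0.50) / 0.15² = 166.6, so 167
- design effect with 8 retained per GP = 1 + 7×0.03 = 1.21
- 167 × 1.21 / 0.80 = 252.6, so 253 per arm

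This is close to 250, so the 20% is a working design input. Up to 0.20 × 500 = 100 patients could have carried values.

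**2. Share of events or changes recorded.** With 12-month risk R and a constant hazard, the risk by month t is r(t) = 1 − (1 − R)^(t/12). At 20% dropout and equal risk, LOCF records 0.80×R + 0.20×(mean r at last contact). For an assumed R = 10%, r(1) = 0.87% and r(6) = 5.13%.

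| Timing of dropout | Recorded | Share of true 10% | Patients missed in 500 |
|---|---|---|---|
| All before month 1 | 8.0% | 80% | 10 |
| Split equally over the three intervals | 8.4% | 84% | 8 |
| All after month 6 | 9.0% | 90% | 5 |

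The shares are almost the same for R from 5% to 30% (80% to 91%). If the hazard doubles after dropout, the share falls to 67% to 85%.

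**3. Sustainability, as change in therapy.** Assume 30% of patients change by 12 months, with dropout split equally: r(1) = 2.93%, r(6) = 16.33%. Recorded changes = 0.80×30 + 0.20×(0 + 2.93 + 16.33)/3 = 25.3%. Therapy appears sustained in 74.7% instead of 70.0%.

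**4. Sustainability, as an arm difference.** As an illustrative worst case, intervention warfarin use is 50% at month 1 and 35% at month 12, control stays at 35%, and 20% have month-1 data only.

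- LOCF at month 12 = 0.80×35 + 0.20×50 = 38%, against 35%: a false 3-point effect
- with the upper 23 points (58% at month 1): 0.80×35 + 0.20×58 = 39.6%, a false 4.6 points
- if only half the effect fades, the overstatement is half as large: 1.5 and 2.3 points

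This needs no imbalance in dropout, because only the intervention arm has an effect to lose.

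**5. Events, as an arm difference.** Assume a true risk of 10% in both arms and equal split over time.

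- 20% dropout in both arms: 8.4% v 8.4%, no false difference
- 20% v 10% dropout: 8.4% v 9.2%, a false difference of about 0.8 points in favour of the arm that loses more patients
- equal 20% dropout after month 6 with true risks of 10% v 8%: about 9.0% v 7.2%, so a true gap of 2.0 points shrinks to 1.8

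**The case against.** Several points on the other side carry weight.

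- **LOCF is only an example.** The rule is therefore open, and a fuller analysis plan may exist. This softens the point. It does not remove it, because the article names no other method and exempts no outcome.
- **Other sources exist.** GP notes and hospital records could recover some events. The article describes them for verifying outcomes or after an admission, not for completing follow-up of patients who withdraw.
- **The 3-point example is extreme.** It combines total loss of effect, month-1 data only for all dropouts, and the full 20% dropout. It also concerns a secondary outcome. The primary therapy outcome tied to the application of the tool should be touched little, since baseline data are collected within 48 hours of the index consultation.

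Four stronger readings are tempting, and the article does not support them.

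- **Every dropout is coded as sustained and event-free.** This is not so: a change, stroke or bleed recorded at month 1 or 6 is carried forward.
- **Confidence intervals are too narrow and the type I error is inflated.** This does not follow for LOCF. Each carried value is that patient's own earlier observation, so the arm mean is still a mean over independent patients, apart from clustering, which the plan adjusts for. A simulation with 250 per arm, 35% in both arms, 20% dropout and month-1 values carried forward (clustering ignored) rejected in 4.8% to 5.1% of runs at a nominal 5%. The problem is bias.
- **The event comparison is tilted towards the tool.** The direction depends on dropout by arm, which is not given. Equal dropout only attenuates a true difference, and since the stated hypothesis is fewer strokes and bleeds, that would work against the tool.
- **For a failure to start, the carried baseline is a post-tool value.** The article does not define the term for patients or for GPs, so this cannot be settled.

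**Conclusion.** The point holds in a limited form, as something that should be fixed before analysis. The only missing-data method named is unsuitable for the sustainability outcome and for the 12-month clotting, bleeding and all-events outcomes, one of which is primary.

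At 20% dropout and equal risk, about 10% to 20% of true events or changes would go unrecorded unless records recover them. The loss is larger if patients who leave are at higher risk. Sustained therapy is overstated where the effect wanes, by up to about 3 points in the worst case built on a 15-point effect. Absolute event rates are biased low in both arms; the bias in the arm comparison is conditional on differential dropout.

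These sizes rest on assumed event and change rates, assumed dropout timing, a constant hazard, and dropout at the planned ceiling. Lower dropout or good recovery from records would reduce them in proportion.

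**What to change.** - **Remove LOCF** from the Data analysis section.
- **Therapy:** analyse status at 1, 6 and 12 months with a cluster-adjusted mixed logistic model on all observed visits, which is valid if data are missing at random. Use multilevel multiple imputation as a sensitivity analysis.
- **Clotting, bleeding and all events:** analyse time to first event, or events per person-time, censored at last contact, with clustering accounted for. Survival analysis is already planned for mortality, so this extends an existing method.
- **Records:** where consent allows, state that the GP notes and hospital records already reviewed will also be used to complete 12-month therapy and event status for patients who miss an interview or withdraw.

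The cost is a change of wording, somewhat more analyst time, and recording a date for each event. Recruitment, visit schedule and sample size stay as they are.
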